The inclusion and exclusion criteria are listed in Table 1. The number of excluded patients and the reasons for exclusion will be recorded. The diagnostic criteria are based on the DSM-V system. Initial assessment will be conducted with independent researchers who will not be involved in the further interventions. It will include a pharmacological consultation by a psychiatrist, personality diagnosis with SCID-II [24, 25], and diagnosis of clinical disorders with the Mini International Neuropsychiatric Interview 5^1^ (MINI) [71, 51]. Diagnosis and evaluation for treatment will be carried out during ambulatory sessions. The focus of the treatment is on psychotherapy, but medication will be continued or initiated if necessary during the screening procedure at least four weeks before the beginning of group psychotherapy (stable medical treatments with selective serotonin re-uptake inhibitors or serotonin-norepinephrine reuptake inhibitors, without dose changes during psychotherapy unless necessary). Baseline measurements and final adjustments of pharmacological treatment will be conducted one day before the beginning of therapy. Randomization will take place during the last diagnostic session. Participants will be randomized using random number tables. A recruitment flow chart is presented in Fig. 1. Patients are planned to be enrolled in the study for over a period of three years. Before participating in the study, each patient will be provided with written information about the study and will be invited to give written consent for inclusion. Participants who do not meet the inclusion criteria will be offered suitable alternative treatment options.

**Table 1 Tab1:** Inclusion and exclusion criteria

Inclusion criteria	Current diagnosis of Axis I anxiety disorder (based on the MINI)
	Diagnosis of comorbid personality disorder (based on the SCID II) or depressive disorder (based on the MINI)
	Aged 18 to 65-years-old
	Sufficient knowledge of the Polish language
	Written informed consent from the patient
Exclusion criteria	Organic brain disorder
	Acute substance-related disorders
	Schizophrenia or bipolar affective disorder
	Severe depression (defined as over 26 points on the Beck Questionnaire)
	Cluster A personality disorders
	Current suicidal ideation and a high risk of suicide
	Restricted intellectual capacity
	Serious unstable medical problems or complications
	Concurrent psychotherapeutic treatment

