### Assessments

Patients are subjected to four assessments: 1) at the screening; 2) at baseline after randomization; 3) at the end of the 12-week treatment; and 4) six months after the end of therapy in order to evaluate the longer-term effects of the treatments. Patients in the wait-list group will have one additional assessment at the end of the 12-week waiting period.

Information from the screening will be used to perform stratified randomization and to validate the inclusion and exclusion criteria. Patients will be assessed by independent and trained clinicians who will remain blind to the treatment conditions, and who will not be involved in direct clinical care of any of the patients. Primary outcome measures and secondary outcome measures can be distinguished in this study. The primary outcome measures include self-report symptoms of anxiety, observer-rated symptoms of anxiety, global improvement, and dichotomized diagnosis of anxiety disorder (improved or unimproved). The secondary outcome measures include personality, depression, self-esteem, defense mechanisms, beliefs about self and others, interpersonal problems, object relations, parental bonding, meta-cognition, and quality of life. The following sociodemographic data will be collected: sex, age, marital status, education, past treatments, symptom history, and medication. We will also examine patients’ expectancy toward change and treatment. Some of the variables, such as the presence or absence of a personality disorder, will be treated in exploratory analyses as predictors and moderators of treatment response. The time points of assessment and measures are presented in Table 3.

**Table 3 Tab3:** Instruments at different assessment points

Instrument	Screening	Baseline	End of Treatment	6-Month Follow-up
STAI		X	X	X
HAM-A		X	X	X
CGI-S		X	X	X
CGI-I		X	X	X
M.I.N.I.	X		X	X
SCID-II	X			
BDI-II	X		X	X
OQ-45		X	X	X
SES		X	X	X
DSQ-40		X	X	X
PBQ		X	X	X
IIP		X	X	X
DWM-S		X	X	X
ECR		X	X	X
BORRTI		X	X	X
MCQ		X	X	X
SWLS		X	X	X
CEQ		X		

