### Statistical analysis

All data analyses will be performed using SPSS Statistics software v21.0 (IBM Corporation, Armonk, NY, USA). All randomized patients will be analyzed, including those who stop receiving treatment, on an intention-to-treat (ITT) as well as treatment-completer basis. The multiple imputation method will be used for missing data when appropriate. Analyses of variance with repeated measures (three measurement points: pre, post, and follow-up) will be applied for continuous data (primary outcomes: STAI, HAM-A, CGI-S, and CGI-I; secondary outcomes: BDI-II, OQ-45, SES, DSQ-40, PBQ, IIP, DWM-S, ECR, BORRTI; MCQ, and SWLS). Primary planned comparison is the interaction between the time (pre-to-post and post-to-follow-up change on anxiety) and group variables (CBT versus wait list; PDT versus wait list). Chi-squared tests will be applied for dichotomous data (MINI). Additionally, random effects models for repeated measures will be used. Multiple regression analyses will be applied to test moderators of change that is to show whether each of the interventions is more effective for some groups of patients (interventions, diagnoses, combination of diagnoses and baseline measurements as predictors). Multiple regression analyses will be also applied to search for mediators of change that are theory-specific (for example, changes in beliefs for CBT and changes in defense mechanisms for psychodynamic therapy). We will take into account to what extent the patients were exposed to the intervention by analyzing the dose-effect relationship.

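### Randomisation is said to be stratified on screening information, but the primary analyses carry no stratum term, so their standard errors may be slightly too large

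*Protocol article*

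**What the plan says.** Allocation is described in two places in the protocol article. The section on recruitment, criteria and randomisation states "Participants will be randomized using random number tables", and gives the timing: "Randomization will take place during the last diagnostic session". The Assessments section adds the scheme: "Information from the screening will be used to perform stratified randomization and to validate the inclusion and exclusion criteria". The first section does not mention strata. The second does not name the factors or their levels.

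The Statistical analysis section defines the main test on the continuous outcomes as follows: "Primary planned comparison is the interaction between the time (pre-to-post and post-to-follow-up change on anxiety) and group variables". The groups compared are CBT against wait list and psychodynamic therapy against wait list. For the diagnosis outcome, which Assessments lists among the primary measures, it says "Chi-squared tests will be applied for dichotomous data (MINI". It also says "Additionally, random effects models for repeated measures will be used", without listing covariates. Separate moderator regressions take "interventions, diagnoses, combination of diagnoses and baseline measurements as predictors". No stratum term appears in the ANOVA or in the chi-squared test.

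**The concern.** When allocation is balanced within strata, differences between strata no longer contribute to chance differences between arms. The treatment estimate is then more precise than under simple randomisation. An analysis without the strata leaves their variance in the error term, so its standard error describes a less precise trial than the one that was run. Intervals are too wide, the test rejects less often than its nominal level, and some power goes unused.

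Two statements in the article therefore need joining: how the strata are used in allocation, and how they are used in analysis. A reader who has only the randomisation section would not know that the design is stratified.

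**Working it through.** **Inputs.** From the Sample size calculation section: alpha 0.05, power 0.80, d = 0.58 for therapy against wait list, f = 0.25 for the interaction, 159 patients in the 3 × 2 plan, 25% dropout, 199 to recruit. Not in the documents, so assumed: R², the share of variance in *change* explained by the strata, taken from 0 to 0.20. I also assume that d = 0.58 is expressed in standard deviations of the change score.

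**The plan's own figures.** A noncentral F calculation with three equal groups and f = 0.25 gives 159. Then 159 × 1.25 = 198.75, rounded up to 199. Stratification does not enter this calculation, so the point changes no stated sample size. The analysed size per arm used below is 159 / 3 = 53.

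**Why R² concerns change.** The primary test is the time-by-group interaction. A stratum difference in level that is constant over time cancels out of change. Only a link between stratum and change can inflate the standard error of this test.

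**Standard error.** Without the stratum term, SE = √(2/53) = 0.1943. Under allocation balanced within strata, the true value is 0.1943 × √(1 − R²). The ratio of the two is 1/√(1 − R²).

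**Power (normal approximation).** Under stratified allocation:
- without the term: Φ[(0.58 − 1.96 × 0.1943) / true SE]
- with the term: Φ[(0.58 − 1.96 × true SE) / true SE]

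| R² for change | True SE | SE too large by | Power without term | Power with term |
|---|---|---|---|---|
| 0 | 0.1943 | 0% | 84.7% | 84.7% |
| 0.01 | 0.1933 | 0.5% | 84.9% | 85.1% |
| 0.05 | 0.1893 | 2.6% | 85.4% | 86.5% |
| 0.10 | 0.1843 | 5.4% | 86.0% | 88.2% |
| 0.20 | 0.1737 | 11.8% | 87.4% | 91.6% |

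The figure of 84.7% is also the power if allocation is simple and no term is fitted.

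**Check by simulation.** The set-up was two arms, 106 patients in total, two strata split 80/20 (an assumption), blocks of 4, and 5,000 runs under no effect. Without the term:

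| R² | Mean reported SE | Actual SE | Type I error |
|---|---|---|---|
| 0 | 0.1935 | 0.1948 | 5.3% |
| 0.05 | 0.1942 | 0.1913 | 4.8% |
| 0.10 | 0.1937 | 0.1831 | 3.8% |
| 0.20 | 0.1940 | 0.1745 | 3.2% |

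With the term, type I error stayed between 5.1% and 5.5%. In 2,500 runs with d = 0.58, power went from 86.2% to 87.0% at R² = 0.05 and from 84.4% to 86.6% at R² = 0.10. With simple allocation and R² = 0.20, the unadjusted standard error was right: 0.1948 reported against 0.1964 actual.

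**The case against.** Much of the case on the other side stands.

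- **Contradiction.** A reader might infer that the two sections contradict each other. They do not. One names the source of random numbers and the other the scheme, and random number tables can be used within strata. Randomisation takes place at the last diagnostic session, when the screening data are available.
- **No blocks.** A reader might also infer that stratification has no effect because no blocks are mentioned. Unrestricted draws within strata would indeed balance nothing, but the article does not say that the draws are unrestricted. Block details are commonly left to a fuller document.
- **No analysis uses the strata.** This cannot be shown. The strata are unnamed, the moderator regressions include diagnoses and baseline measurements, and the random-effects models may carry covariates listed elsewhere. Those regressions do not correct the primary test, however, so the narrower statement about the ANOVA and chi-squared test holds.
- **Size and direction.** The effect depends on an R² that the documents do not give. It is small at plausible values, and its direction is conservative, so it creates no false-positive risk.
- **Logistic regression for MINI.** A chi-squared test remains valid, if conservative. A stratum-adjusted odds ratio is conditional on stratum and so is a different quantity from the unadjusted one. The choice of effect measure should be deliberate.

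These objections do not remove the point that the plan states a stratified design and states primary tests that do not use it.

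**Conclusion.** The point holds as a modest improvement to a stated method. The primary analyses as written have no stratum term although randomisation is said to be stratified. If allocation is balanced within strata that explain 5% to 10% of the variance in change, the standard errors are about 3% to 5% too large. Power at d = 0.58 with 53 per arm would then move from about 85% to 86–88%. Against an unadjusted test in the same stratified trial, the stratum term contributes 1.1 points (85.4% to 86.5%) at R² = 0.05 and 2.2 points (86.0% to 88.2%) at R² = 0.10.

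The estimate is not biased in either case. It would also be wrong to conclude that the benefit of stratifying is lost. The balance between arms and the true precision remain, and only the reported standard error and p value fail to reflect them. If allocation proves to be simple, or if the strata predict severity but not change, the standard error of the time-by-group test is not inflated.

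**What to change.** 1. Replace the two descriptions of allocation with one statement, repeated or cross-referenced in both sections: the random number tables are used to form restricted allocation (for example permuted blocks) within strata, and the stratification factors and their levels are named.
2. In the primary repeated-measures model and the random-effects models, include the stratification factors **and their interaction with time**. A stratum main effect alone does not touch the time-by-group test.
3. For MINI, use a stratum-adjusted analysis, such as Cochran-Mantel-Haenszel or logistic regression with arm and strata, and say which effect measure will be reported.

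The cost is wording and a few model terms. No new data or patients are needed, and the Trial status section says that recruitment is still to begin.

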### Interventions

Interventions will be offered in a daily unit setting, which is a part of the Wola Center for Mental Health at the district Wola Hospital in Warsaw. Psychodynamic and cognitive-behavioral group psychotherapy has been provided at the Wola Center since 2011. This method was developed by the current team during the last ten years in another clinical setting. When the research project starts, each group therapy will be conducted by two therapists trained in accredited cognitive-behavioral or psychodynamic/psychoanalytic therapy programs.

As is stated in the informed consent, patients will be encouraged not to commence any other therapy in the six-month period after the treatment. In cases of acute deterioration, crisis intervention will be offered. Due to ethical reasons we decided not to ask for postponing other therapy when it seems to be needed. Further treatment choices of the patients will not be controlled.

### Short-term intensive psychodynamic group therapy versus cognitive-behavioral group therapy

Both modality therapists should have at least three years’ experience in working with groups. Comprehensive treatment manuals prepared by a group of current and past members of the department’s therapeutic team, who were personally involved in the study, will be used for both treatments. The two treatments will be delivered at the same levels of frequency, defined by the total number of sessions over the study period. The number of spoken group therapy sessions lasting 90 minutes for each treatment modality will total 70 to 80 hours over a period of 12 weeks. This is the maximal period of time that can be reimbursed by insurance companies. Both approaches will contain additional interventions: psycho-drawing (one session per week), movie therapy (one session per week), and relaxation training (one session per week; see the treatment weekly schedule in Table 2). They are parts of both manuals and are aimed to intensify the therapeutic processes.

**Table 2 Tab2:** Treatment weekly schedule

Time^a^	Monday	Tuesday	Wednesday	Thursday	Friday
9:00-10:30	Psychotherapy	Relaxation	Movie therapy	Psycho-drawing	Psychotherapy
	1 hour 30 minutes	1 hour 30 minutes	1 hour 45 minutes	1 hour 30 minutes	1 hour 30 minutes
10:30-11:15	Meal break	Meal break	Meal break	Meal break	Meal break
	45 minutes	45 minutes	45 minutes	45 minutes	45 minutes
11:15-12:45	Psychotherapy	Psychotherapy	Movie therapy	Psychotherapy	Psychotherapy
	1 hour 30 minutes	1 hour 30 minutes	1 hour	1 hour 30 minutes	1 hour 30 minutes
13:00-13:50	50-minute psychiatrist group consultations				

^a^Patients come to the hospital between 8 and 9 am and leave between 1 and 2 pm every day

Treatment will start in the morning hours and end in the afternoon. According to the Polish health care regulations, patients treated in a day hospital setting should have a therapeutic program for at least five hours a day. This study will be conducted in closed-ended groups. The hospital will provide a small meal during the 45-minute break between the two 90-minute psychotherapy sessions. The acceptable limit of absences is five days throughout the whole treatment. Psychotherapists will receive weekly supervision by certified supervisors. All spoken psychotherapy sessions will be recorded, and a random selection of 10 % from each therapy will be analyzed by two different independent raters on protocol adherence. This will ensure that the essential ingredients are being covered by the therapist and, if not, then the reason for the deviation will be recorded. The reported deviation will be considered minor or major by the principal investigator, who will decide if the particular group should be excluded from the study. The Comparative Psychotherapy Process Scale (CPPS) [34] will be used for this purpose, together with *ad-hoc* checklists based on specific group treatment manuals. The CPPS is designed to assess the distinctive features of psychodynamic-interpersonal and cognitive-behavioral treatments.

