### Participant recruitment, inclusion and exclusion criteria and randomization

Participants with anxiety disorders and comorbid personality disorders will be recruited from an outpatient clinic. Participation is voluntary. Informed consent is given in writing and signed with a personal signature. Participants may withdraw their informed consent at any time, without any consequences for their treatment. Randomization will take place after informed consent has been obtained. Subjects who meet all of the inclusion criteria will be randomized to two modalities of treatments or to the wait list.

Patients from the wait list will continue pharmacological treatment and will take part in monthly supportive consultations. Crisis intervention will be offered when needed. In accordance with the informed consent procedure, patients will not receive treatment in another clinic while waiting for day-treatment care. After the waiting period they will be randomized into two intervention groups.

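### The principal investigator may exclude whole therapy groups on adherence after randomisation, which, if used, conflicts with the rule that all randomised patients are analysed

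*Protocol article*

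**What the plan says.** The fidelity procedure stands in the intervention section that compares the two therapies. Spoken sessions are recorded, and "a random selection of 10 % from each therapy will be analyzed by two different independent raters on protocol adherence". The principal investigator then grades any deviation as minor or major and is the person "who will decide if the particular group should be excluded from the study". The passage gives no criterion for the grade or for the exclusion, and it names no analysis set.

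The Statistical analysis section sets the analysis rule: "All randomized patients will be analyzed, including those who stop receiving treatment, on an intention-to-treat (ITT) as well as treatment-completer basis". Its primary planned comparison is the interaction of time with "group variables (CBT versus wait list; PDT versus wait list".

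Two statements in the section on recruitment and randomisation fix the order of events and the care of the control arm. On timing: "Randomization will take place during the last diagnostic session". On the control arm: "Patients from the wait list will continue pharmacological treatment and will take part in monthly supportive consultations".

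**The concern.** Removing patients for something that happened after they were randomised undoes the comparability that randomisation gave, unless the removal is unrelated to outcome. Here the unit removed is a whole therapy group, the trigger is how therapy was delivered, and the decision is discretionary. The wait list has no matching mechanism, so each primary contrast would set a possibly trimmed therapy arm against an untrimmed control arm. If the option were used more in one modality than in the other, the comparison of the two therapies (the second objective) would be affected as well.

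This is not a detail left to a later document. The article states two rules that give different analysis populations once the first is applied. A reader of the results could not tell which one had governed them.

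**Working it through.** **1. The passages side by side.**

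- Randomisation takes place at the last diagnostic session, before therapy starts. Every patient in a therapy group has therefore been randomised.
- Adherence is rated on recorded therapy sessions, so the information behind an exclusion arises after randomisation.
- The exclusion is from the study. It is not worded as exclusion from the completer analysis.
- The analysis rule covers all randomised patients. Multiple imputation is planned for missing data, but it does not bring back patients who have been taken out of the study.
- During the 12-week wait, control patients have medication and monthly consultations and no group therapy. They cannot be removed by this rule in that period.

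If the option is never used, the rules are compatible. If it is used once, at least one randomised group is no longer in the study and the analysis rule is not met.

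**2. The plan's own figures.** No figure is attached to the exclusion rule. The recruitment target carries an allowance for dropout only: 159 × 1.25 = 198.75, that is 199. Excluded groups are not mentioned there.

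**3. Share of an arm lost (illustration).** Group size and allocation ratio are not given. Assume equal allocation, 199 / 3 ≈ 66 per arm, and 6 to 12 patients per group.

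- One group of 6: 6 / 66 = 9%
- One group of 12: 12 / 66 = 18%

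**4. Shift in the arm mean (illustration).** Let p be the share removed and D the difference between the mean of the remaining patients and the mean of the excluded group. The full-arm mean is (1 − p) × remaining mean + p × excluded mean. Dropping the group therefore moves the arm mean by p × D. The article gives no value for D, so a range is shown:

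| D (SD) | p = 6/66 | p = 12/66 |
|---|---|---|
| 0 | 0 | 0 |
| 0.5 | 0.045 | 0.091 |

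The upper corner is 0.091 / 0.58 ≈ 16% of the effect of 0.58 planned against wait list. A negative D, where the excluded group did better, would shift the mean against therapy.

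**5. Effect of selecting the worst-rated group (illustration).** A simulation with no true effect dropped the one worst-rated group, from 8 groups of 8 or from 6 groups of 11. The intraclass correlation ran from 0 to 0.1, and the correlation between the adherence judgement and the group's mean outcome was 0.5 or 1.0. The arm mean moved by about 0.04 to 0.11 SD in favour of therapy. The movement comes from the assumed correlation; with none, the expected shift is zero.

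**The case against.** The strongest reply is that the fidelity paragraph is about treatment delivery and is only permissive, whereas the Statistical analysis section is the rule for analysis and names two bases, intention-to-treat and treatment-completer. Excluded groups might leave only the completer set. The wording does not support this. The exclusion is from the study, and the analysis section links adherence ratings to neither set. What stands is that the conflict is contingent: nothing is broken until the option is used.

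A reader might also infer that the rule inflates both therapy-versus-wait-list effects. The article does not show that. The adherence scale measures features that distinguish the two modalities, and the checklists follow the manuals. A group could score poorly because its therapists drifted towards the other approach, and no passage ties low adherence to worse outcome. Upward bias is plausible, but it is not established.

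A reader might further infer that the principal investigator decides with knowledge of outcomes. The article is silent on this and on when the decision falls relative to outcome data. A condensed article may leave such detail to the full protocol, so the silence is not counted as a fault here.

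The illustrated share of an arm also has a caveat. Wait-list patients are randomised to the two therapies after waiting. If they join the same groups, part of an excluded group would not belong to the arm as first randomised, and the share lost from that arm would be smaller.

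**Conclusion.** The conflict between the two stated rules is real and should be resolved before recruitment. It takes effect only if a group is excluded, and during the waiting period only the therapy arms are exposed. The primary contrasts would then no longer rest on the groups as randomised.

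Neither the direction nor the size of any resulting bias can be read from the article. The figures of 9 to 18% of an arm and 0 to 0.09 SD for one excluded group rest on assumed equal allocation, assumed group sizes of 6 to 12 and an assumed difference of 0 to 0.5 SD. They show scale and are not estimates. It would go too far to say that randomisation is already broken, or that the therapy effects will be overstated by a given amount.

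**What to change.** Replace the exclusion rule in the fidelity paragraph with a statement to this effect: every randomised patient stays in the study, is followed up at the planned assessments and is included in the intention-to-treat analysis whatever the adherence rating of the group. Adherence ratings define only a secondary per-protocol or sensitivity set. That set is fixed from the independent raters' scores, without access to outcome data and before any outcome analysis. Add a matching clause to the Statistical analysis section so that both places name the same populations.

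The cost is a sentence or two of text. Session recording, the independent raters and the follow-up assessments are already planned, so no extra staff or data collection is needed.
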